### Setting

VHA primary care uses a multi-disciplinary patient-centered team-based approach (Patient-Aligned Care Teams; PACTs) where teams of health care professionals provide longitudinal care to a panel of patients [35]. Team members include a primary care provider, nurses, clerk, integrated mental health provider, social worker, and a pharmacist. Teams have access to multiple dashboards and reports for care management, including the Care Assessment Need (CAN) score [54], which describes the patient’s risk for future VA hospitalization or death by percentile.

### EBQI activities

We first engaged regional and local multidisciplinary stakeholders to discuss implementation of each EBP, such as the target patient population and the clinical staff who might perform the assessment, developing a “QI Roadmap.” QI training and practice facilitation spans 18 months of video calls with site clinical champions, selected by their facility leadership. Meetings are led by a trained RIVET external facilitator and include structured QI didactics, designing Plan-Do-Study-Act cycles, coaching, review of data, and developing structured action plans (Fig. 1). The RIVET implementation team provides quarterly data reports and regularly discuss next steps with the champions.

The same structured QI didactics are utilized for both LC and IC groups (Fig. 1). The IC sites participate in individual meetings with the clinical champions every month, on average. Learning collaboratives consist of three EBQI-LC sites that participate in monthly meetings. All sites randomly assigned to EBQI-LC participate in the same learning collaborative regardless of EBP (CACP vs MAA), as both EBPs involve the same goal, the same target population, in the same clinical setting, similar to prior initiatives [17, 31, 55].

### Data sources

Data sources include VHA Central Data Warehouse (CDW) administrative data, surveys to high-risk patients, surveys to Primary Care staff, key stakeholder interviews, implementation facilitation logs, time activity surveys, and site administrative documents.

#### EHR Administrative data

VHA CDW contains data on patient characteristics, outpatient encounters, provider types for each encounter, acute and inpatient care utilization, medication fill history, and Healthcare Effectiveness Data and Information Set (HEDIS) quality metric status. Health factor administrative data is generated by templates constructed for each EBP within the EHR. Managerial Cost Accounting (MCA) data will be utilized for the cost analyses.

#### High-risk patient surveys

Patient surveys will collect data on patient experiences among high-risk primary care patients at participating sites. Patient surveys will be mailed at the beginning and end of the 18-month active implementation phase to 500 randomly selected high-risk patients empaneled to primary care teams at each site, sampled cross-sectionally at each time period with replacement. Patient eligibility is based on the following criteria: a Care Assessment Need (CAN) score ≥ 90th percentile within the month prior to the sampling date; a visit with primary care within the last six months of the sampling date; and empanelment to the clinical champion team’s panel. When possible, patient experience and satisfaction questions were sourced from the Patient-Centered Medical Home (PCMH) version of the VHA Survey of Healthcare Experiences of Patients (SHEP), based on the Consumer Assessment of Healthcare Providers and Systems (CAHPS). Additional survey items measure direct impacts of specific EBPs (such as medication adherence), and items that may impact patient engagement in and benefit from EBPs, such as trust in their primary care provider (PCP). See Table 1 for details on included measures.

**Table 1 Tab1:** RIVET QUERI patient survey measures

Measure	Source
Comprehensiveness of Care	SHEP-PCMH [56]
Care Coordination	SHEP-PCMH [56]
Self-Management Support	SHEP-PCMH [56]
Providers Discuss Medication Decisions	SHEP-PCMH [56]
Comprehensive Medication Review	One item from 3-item SHEP-PCMH Care Coordination measure [56]
Discuss Medication Adherence Strategies	Created for RIVET
Medication Adherence	Voils Medication Adherence Scale [57]
Trust in Provider	VA PACT Intensive Management (PIM) High-Risk Patient Survey [58]
Respected by Provider	VA PACT Intensive Management (PIM) High-Risk Patient Survey [58]
Satisfaction with Provider	SHEP-PCMH [56]
Satisfaction with Primary Care Clinic	Adapted from SHEP-PMCH Provider question, used in previous VA studies [59]
Patient Functional Status	NIH PROMIS Short Form Physical Function 4a measure [60]
Patient Health Literacy	Limited Health Literacy screener [61]
Social Support	From CMS Accountable Health Communities Tool [62] and Kaiser Permanente Health Assessment Questionnaire ahcm-screeningtool.pdf (cms.gov)
Social Isolation	From CMS Accountable Health Communities Tool [62] and AARP Loneliness and Connections Survey [63]
Family/Caregiver involved in medical care	Used in previous studies including with Veterans [59, 64]

*SHEP-PCMH* VA Survey of Healthcare Experiences of Patients, Patient-Centered Medical Home Version, *RIVET* High-RIsk VETerans, *PACT* Patient-Aligned Care Team, *NIH* National Institute of Health, *PROMIS* The Patient-Reported Outcomes Measurement Information System, CMS. AARP

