### Site selection and eligibility

We will implement the EBPs at 16 primary care sites, targeting those with high ambulatory care-sensitive hospitalization rates. Each site will be implementing a single EBP. Implementation strategies are randomized by site. Site implementation consists of four overlapping cohorts of four sites (three randomized to LC and one to IC); all will undergo 18-months of RIVET facilitation (see Figure#1). Time periods without active implementation will serve as the usual care periods for EBQI strategies. Usual care sites will receive Office of Primary Care educational campaigns and dissemination of tools for high-risk patients among primary care teams. VHA regional leaders or VHA facility leaders will select the EBP for primary care sites to implement.

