#### Clinical staff surveys

Clinical staff surveys will be administered site-wide, to assess factors that may influence update of RIVET EBPs at the clinic, 1) other tools, resources and practices used when managing high-risk patients, and 2) exposure to RIVET EBPs (post-implementation only), and 3) confidence with practices promoted by RIVET EBPs and with overall high-risk patient care. Most items were derived from previous VA primary care staff surveys, including those conducted for the purposes of evaluating staff experiences and approaches to high-risk patient care [65]. Electronic surveys will be sent to all primary care providers, nurses, and medical assistants on eligible teams at participating sites at the beginning and end of the 18-month active implementation phase. Eligible teams include general and women’s health primary care teams, as well as any ‘specialty’ primary care teams (e.g., geriatric primary care) that the site’s champion considers eligible for EBP spread. Clinician eligibility criteria includes being a member of at least one PACT teamlet at the RIVET site; being either a physician, physician assistant, nurse practitioner, registered nurse, licensed practical or vocational nurse, a medical assistant, or a health technician; providing direct patient care at the site; and working at the primary care site for at least three months.

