## Outcomes and data analyses

To analyze our primary outcome, receipt of each EBP among top 10th percentile high-risk patients during the 18-month implementation period (Reach), we will model uptake of both practices in our Concurrent Stepped Wedge Design as a multilevel hierarchical model with a repeated cross-sectional data structure in which sites are followed over time. In this design, the data structure includes patients at level 1 (where Reach, the main outcome of interest, in measured), nested within time at level 2, and nested within sites at level 3. The main predictors will be site implementation strategy assignment (EBQI-IC vs. EBQI-LC vs Usual Care) over time (measure as the number of quarter). We will first describe differences in trends using unadjusted analyses, then add covariates for patient characteristics (i.e., age, sex, Elixhauser comorbidity score [66]) and site-level covariates (i.e., number of unique patients served in primary care, rural vs urban). Secondary analyses of Reach will include models by key patient subgroups, including those hospitalized in the 90 days prior to the quarter examined, and models with an interaction term for assigned implementation strategy by EBQI fidelity level (as defined above), to examine how implementation strategy fidelity may have impacted Reach.

To analyze our secondary outcomes of care processes, patient experiences, provider experiences, and performance measures (Effectiveness), we will first model unadjusted trends in outcomes over time for each EBP, by site implementation strategy assignment. We will then model outcomes using two or three-level (depending on whether the metric is measured at the patient or site level) hierarchical models based on the concurrent Stepped Wedge Design using repeated cross-sectional data, adjusted for the same covariates included in the models for our primary outcome. In models of medication adherence, we will add covariates for medication regimen complexity, as indicated by total number of classes of medication prescribed for the condition of interest, and patient co-pay status. If we find differences in outcomes, we will perform mediation analyses that consider how Reach and EBP fidelity may have mediated outcomes [67].

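### With surveys only at the start and end of each site's own 18 months, an EBQI-versus-usual-care effect on survey outcomes can rest only on comparisons between cohorts; IC versus LC stays sound

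*Protocol article*

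**What the plan says.** **Timing.** In the protocol article, High-risk patient surveys: "Patient surveys will be mailed at the beginning and end of the 18-month active implementation phase". The sample at each wave is "500 randomly selected high-risk patients empaneled to primary care teams at each site, sampled cross-sectionally at each time period with replacement". Clinical staff surveys has the same schedule: "at the beginning and end of the 18-month active implementation phase". No other survey wave is described, and none at sites still waiting to start.

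**Design.** Site selection and eligibility describes four overlapping cohorts of four sites, each with three LC sites and one IC site, and states: "Implementation strategies are randomized by site". It defines the comparator thus: "Time periods without active implementation will serve as the usual care periods for EBQI strategies". Randomisation of cohort order or start date is not mentioned.

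**Analysis.** Outcomes and data analyses places patient and provider experience among the secondary outcomes, to be modelled with "hierarchical models based on the concurrent Stepped Wedge Design using repeated cross-sectional data". The three-way contrast of IC, LC and usual care, with time counted in quarters, is written out for Reach. The Analysis paragraph of the Abstract describes the trial as a whole as testing IC against LC against usual care.

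**The concern.** A stepped wedge separates an intervention effect from calendar time by observing some sites under usual care while others are already exposed. The survey schedule supplies almost none of this. Each site's only usual-care survey is its own baseline, and its only exposed survey comes 18 months later.

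Drift over such a period is plausible on the article's own account. The Discussion names staffing changes, new health-system initiatives and pandemic-related changes in care delivery, and usual-care sites also receive national primary care campaigns. A stepped-wedge model fitted to these data could print an EBQI effect on patient or staff experience that is partly or wholly such drift. The outcomes at stake are the survey-based entries of Table 2, such as comprehensiveness of care, self-management support, survey-reported medication adherence and provider experience.

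**Working it through.** The article gives no figure to reproduce, so the check asks which contrasts can be estimated.

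**Inputs from the article.** 4 cohorts × 4 sites = 16 sites: 4 IC and 12 LC. Two waves per site give 32 site-waves, and 16 × 500 × 2 = 16,000 patient surveys mailed.

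**Assumptions.** The spacing between cohort starts is not in the text (the figure is not shown), so 3, 4, 6, 9 and 12 months were tried. Standard errors are in SD units and assume ICC 0.03, cluster autocorrelation 0.8 and 200 respondents per site-wave.

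**1. Within a site.** For a site starting at time s, with effect θ and common time function f:

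- change = θ + f(s + 18) − f(s)

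Every site has the same form. If f is linear with drift δ per 18 months, every change equals θ + δ, and only the sum is identified. In matrix form, 16 site terms + 1 linear time term + 2 treatment terms = 19 columns. Calendar time equals the site's start date plus 18 × (IC + LC), which is one exact dependency, so the rank is 18. IC and LC versus usual care are not estimable at any spacing. Categorical time gives the same answer, because it includes the linear trend.

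**2. Random site effects, categorical time.** A usual-care contrast now needs one cohort's end wave to fall on a later cohort's start wave. With spacing g and four cohorts, this requires 18 = g, 2g or 3g. Among the spacings tried, that means 6 months (one shared date) and 9 months (two).

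**3. Random site effects, linear time.** The contrast is always estimable, because the slope comes from comparing cohorts surveyed at different dates.

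| Spacing (months) | LC v usual care, site fixed effects | LC v usual care, random sites, categorical time: SE | LC v usual care, random sites, linear time: SE |
|---|---|---|---|
| 3 | not estimable | not estimable | 0.234 |
| 4 | not estimable | not estimable | 0.178 |
| 6 | not estimable | 0.133 | 0.122 |
| 9 | not estimable | 0.095 | 0.087 |
| 12 | not estimable | not estimable | 0.071 |

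IC versus usual care follows the same pattern, with SE 0.090 to 0.240 under linear time.

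**4. IC versus LC.** Sites in a cohort are surveyed at the same times, so common drift cancels.

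- Variance of one site's change = 2 × [(1 − 0.03)/200 + 0.03 × (1 − 0.8)] = 2 × (0.00485 + 0.006) = 0.0217
- Variance of the IC−LC difference = 0.0217 × (1/4 + 1/12) = 0.00723, so SE = 0.085

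With random site effects, which also use the baseline level, the SE is 0.078. Both hold at every spacing.

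**5. For comparison.** If each site were surveyed at every calendar wave up to its own end date, both usual-care contrasts would be estimable in all 20 scenarios (5 spacings × 2 time forms × 2 site-effect forms). SEs would be 0.038 to 0.049 for LC and 0.051 to 0.064 for IC. Part of that gain comes simply from having more surveys.

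**The case against.** **The planned model is hierarchical.** The fixed-effects result is therefore not the whole answer. A reader might infer that the survey data can give no EBQI-versus-usual-care estimate at all. The documents do not support that: with random sites, a linear trend yields an estimate at every spacing, and counting time in quarters can be read as linear. This limits the point, but the estimate then leans on cohorts being exchangeable and on the assumed trend. Silence about cohort order does not show that it was not randomised. Equally, nothing in the article lets a reader rely on it.

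**The usual-care contrast is spelled out only for Reach.** This is correct, and no sentence promises a usual-care effect on patient or staff experience. It is nevertheless the natural reading of a model based on the stepped wedge, in a trial described as testing both strategies against usual care.

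**SHEP may be a second source.** Table 2 labels several items as patient survey or SHEP. Routine SHEP data could supply concurrent usual-care observations. However, Data sources lists no such feed, and the patient survey section treats SHEP as a source of questions. The ambiguity stands and limits which outcomes the fix covers.

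**Details may sit in an unseen analysis plan.** An analysis plan could settle the time term and the site effects, but it would not supply survey waves that the stated schedule lacks. The mismatch is between two things the article does state.

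**Conclusion.** The point holds for outcomes measured only by the study's patient and staff surveys. Within sites, exposure and 18 months of secular change are fully confounded. Any usual-care contrast is a between-cohort comparison, not described as randomised, and it depends on random site effects plus either a linear trend or coinciding waves. Its precision varies widely with the unknown spacing: the LC standard error runs from 0.071 to 0.234 SD under the assumed ICC, autocorrelation and response. The estimability results do not depend on those three assumptions.

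A reader might also infer that the main strategy comparison or the primary outcome is compromised. Neither is. IC versus LC is randomised, estimable in every scenario and protected from common secular change. Reach and the other administrative outcomes do not depend on the two survey waves.

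**What to change.** For outcomes measured only by the study's patient and staff surveys:

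- Make the IC-versus-LC difference in pre-to-post change the inferential contrast. Use a hierarchical model with wave, cohort, strategy-by-wave and the covariates already planned, and a small-sample correction suited to 4 IC and 12 LC sites.
- Report each arm's pre-to-post change, and any usual-care contrast from the model, as uncontrolled and exploratory.

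Keep the stepped-wedge usual-care contrast for quarterly administrative outcomes. Apply it to a SHEP item only if routine SHEP data are actually available at concurrent calendar times, and say which Table 2 items those are.

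This changes analysis wording only. The cost is that the usual-care claim for survey outcomes becomes descriptive. If that claim matters to the sponsor, the alternative is to survey waiting sites at the other cohorts' wave dates as well, at the price of more mailings and staff surveys.

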#### Clinical staff surveys

Clinical staff surveys will be administered site-wide, to assess factors that may influence update of RIVET EBPs at the clinic, 1) other tools, resources and practices used when managing high-risk patients, and 2) exposure to RIVET EBPs (post-implementation only), and 3) confidence with practices promoted by RIVET EBPs and with overall high-risk patient care. Most items were derived from previous VA primary care staff surveys, including those conducted for the purposes of evaluating staff experiences and approaches to high-risk patient care [65]. Electronic surveys will be sent to all primary care providers, nurses, and medical assistants on eligible teams at participating sites at the beginning and end of the 18-month active implementation phase. Eligible teams include general and women’s health primary care teams, as well as any ‘specialty’ primary care teams (e.g., geriatric primary care) that the site’s champion considers eligible for EBP spread. Clinician eligibility criteria includes being a member of at least one PACT teamlet at the RIVET site; being either a physician, physician assistant, nurse practitioner, registered nurse, licensed practical or vocational nurse, a medical assistant, or a health technician; providing direct patient care at the site; and working at the primary care site for at least three months.

#### Key stakeholder interviews

Guided by the Practical, Robust Implementation and Sustainability Model (PRISM) and Consolidated Framework for Implementation Research (CFIR) frameworks, we will conduct pre- and post- semi-structured qualitative telephone interviews with key middle managers (Primary Care Medical Director, Primary Care Nursing lead, Social Work lead, Integrated Mental Health lead, Pharmacy lead) and frontline clinicians who participate in EBQI and implementation activities. The interviews will assess readiness (inner context) and its subconstructs of leadership and engagement, available resources, and access to knowledge and information; implementation climate (inner context) and its subconstructs of relative priority and values; implementation process and its subconstructs of engaging key stakeholders and executing the implementation plan; characteristics of Individuals and its subconstruct of knowledge and beliefs about the intervention; and intervention characteristics and its subconstructs of relative advantage and complexity.

#### Implementation facilitation logs

We will use templated implementation facilitation logs to collect information about participants’ attendance at EBQI activities (including facilitation sessions and other meetings), participants’ role in RIVET, plan-do-study-act cycles, ‘real time’ adaptations to the EBPs, and barriers to implementation. The Implementation facilitators and coordinator will complete the implementation facilitation logs for both EBQI-IC and EBQI-LC sites after each meeting and any contact with implementation sites and leadership.

#### Time activity surveys

We will administer weekly time surveys to the RIVET implementation team which will capture RIVET staff time spent in various implementation activities. To assess time spent on RIVET implementation activities by site participants outside of facilitation sessions and other meetings with the RIVET implementation team, we will conduct brief monthly polls via Teams during facilitation sessions.

#### Periodic reflections

Using a semi-structured interview guide, a 30-min recorded monthly meeting will be conducted with the facilitation staff to elicit information and their overall impression of implementation progress and process. The meeting will document any implementation challenges and successes, adaptations, stakeholder engagement and relevant contextual issues. We will assess contextual factors, such as organizational readiness (leadership engagement, resources, access to knowledge and information) and anticipated barriers/facilitators at each site.

#### LC and IC site administrative documents

The site administrative documents include the QI roadmap for each EBP, site action plans developed by clinical champions, meeting minutes, written reports and presentations to leadership, and attendance records.

### Measures

The Practical, Robust Implementation and Sustainability Model (PRISM) framework) [33, 34] will guide the planning, implementation, and evaluation of the RIVET Program. The PRISM framework specifies contextual factors which align well with the components of our implementation strategies, and which will guide our evaluation of factors that influence Reach, Effectiveness, Adoption, Implementation, and Maintenance (RE-AIM) outcomes [34]. We will use mixed methods to evaluate RE-AIM outcomes, EBP fidelity, implementation strategy fidelity, adaptations, costs, benefits, and value.

#### Reach

Reach is defined in this study as the proportion of high-risk patients on each study team’s panel that received one of the EBPs during the 18-month implementation period. See Table 2 for details on included reach measures. We define “high-risk patients” using a VHA-specific risk score called the Care Assessment Need score, previously developed and validated by VA through machine-learning to predict a patient’s risk for a VHA hospitalization or mortality [54]. We define ‘receipt’ as having the EBP assessment at least partially documented in the electronic health record (EHR). We will also examine the patient characteristics (sociodemographic, Elixhauser comorbidity score [66]) of eligible patients who did vs. did not receive the EBP.

**Table 2 Tab2:** Reach and effectiveness outcomes metrics

	**Reach** **(Primary Outcome)**	**Proximal Care Process Impacts**	**Patient and Provider Impacts**	**Clinical Quality and Outcomes**
EBP 1 CACP	Proportion of site-assigned patients in the top 10% of CAN-hospitalization scores that receive the EBP	• Number and type of referrals generated • Referrals completed by patient • Number of primary care social worker, pharmacist, nurse, integrated MH encounters	• Comprehensiveness of Care (Patient Survey^a^/SHEP) • Self-Management Support (Patient Survey^a^/SHEP) • Primary Care provider experience and perceived support for high-risk patient care (Clinician Survey)	• VHA ACS-related and total acute hospitalizations • VHA ACS-related and total emergency department visits
EBP 2 MAA		• Number and type of referrals or actions documented receiving the EBP • Number of primary care pharmacist, social worker, nurse, integrated MH encounters	• Providers Discuss Medication Decisions/Medication Comprehensiveness (Patient Survey^a^/SHEP) • Self-Management Support (Patient Survey^a^/SHEP)	• Medication adherence (Patient Survey^a^) • Adherence for DM, HTN, HL, MH medications (VHA Pharmacy Data) • HEDIS measures for DM, HTN, HL management

*ACS* Ambulatory care-sensitive, *EBP* Evidence-based practice, *CACP* Comprehensive Assessment and Care Planning, *CAN* Care Assessment Need, *DM* diabetes mellitus, *HTN* hypertension, *HEDIS* Healthcare Effectiveness Data and Information Set, *HL* hyperlipidemia, *MAA* Medication Adherence Assessment, *MH* Mental Health, *PDC* proportion of days covered, *SHEP* Survey of Healthcare Experiences of Patients

^a^Refers to patient survey referenced in the Methods

